### Missing data from scans not done before or after randomisation

Not all trial patients will be scanned before and after randomisation. We will report the number of patients without scans
^28^ and baseline data for patients included in the analysis to help identify any selective missingness of outcomes by treatment arm
^32^. We will examine whether missing scans are missing equally between treatment arms and appear to be missing completely at random (MCAR). In this case, although missing data reduces the precision of the analysis, it does not bias the treatment effect
^33^.

However, if haemorrhage expansion is associated with the reason the data are missing (patients with haemorrhage expansion may die before the second scan, patients without haemorrhage may not need to be re-scanned), imbalance in missing data by treatment arm can cause bias. We will examine whether the occurrence of missing scans is influenced by fully observed baseline variables (e.g. GCS), using relative risks and 95% confidence intervals estimated using generalised linear models. If they are, and within defined groups data are missing completely at random, the data could be missing at random (MAR)
^33^. For example, if missingness depends on GCS, but within mild, moderate and severe GCS groups missingness is unrelated to haemorrhage or infarction, the data are MAR. In this case, a regression analysis which takes GCS group into account should give unbiased estimates of the treatment effect
^34^.

However, we suspect that within GCS groups, missingness could be related to haemorrhage volume (i.e. low GCS patients are expected to have a greater haemorrhage volume than high GCS patients). In this case, the data would be missing not at random (MNAR) (i.e. even when accounting for the fully observed data, the reason for missing observations still depends on the unseen values)
^33^.

Because injury severity can partly explain missingness and there are unknown reasons for some missingness, it is difficult to confirm whether our missing data will be MAR or MNAR. For the purpose of the primary analysis, we will assume missing data are MAR. To examine how robust the primary analysis is to the chosen method of handling missing data, we will conduct sensitivity analyses assuming missing data are MCAR or MNAR. Under the MCAR assumption, we will compare haemorrhage volumes between treatment groups without accounting for missingness. Under the MNAR assumption, we will compare haemorrhage volumes between treatment groups and explore the possibility that missingness of the outcome data is related to prognostic characteristics as well as to the trial treatment. If tranexamic acid reduces intracranial haemorrhage expansion and the risk of death, patients who receive tranexamic acid may be more likely to be scanned post-randomisation compared to those who receive placebo. On the other hand, if tranexamic acid reduces or prevents intracranial haemorrhage expansion, post-randomisation scanning may not be clinically indicated in these patients. We will conduct sensitivity analyses excluding patients with a low pre-randomisation GCS who may have large haemorrhage expansion and therefore not survive to have a post-randomisation scan. We will conduct sensitivity analyses excluding patients with a high pre-randomisation GCS who may have smaller haemorrhage expansion and therefore not require a post-randomisation scan.

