### Primary analysis

Linear mixed model
^26^ will be used to compare the mean change in intra-parenchymal haemorrhage volume from pre- to post-randomisation between treatment groups. The basic model includes pre- and post-randomisation volumes as correlated outcomes with mean post-randomisation volumes allowed to differ by treatment group but mean pre-randomisation volumes constrained to be the same, and with variances of pre- and post-randomisation volumes allowed to differ. In the absence of missing data, this linear mixed model gives identical estimates of the treatment effect, and near identical standard errors to the more standard ANCOVA analysis. The advantage of the linear mixed model approach is that patients with missing pre- or post-randomisation scans can be included in the analysis, potentially reducing bias and increasing efficiency
^26^.

A linear regression analysis of the blinded data indicated that time from injury to CT scan, GCS, age and systolic blood pressure are significantly predictive of the pre- and post-randomisation bleeding volumes (p<0.05). These covariates and the stratification factor (hospital site)
^27^ will be included in the analysis to improve the precision of the effect estimate. The main effect of site (which is treated as fixed) is accounted for in the model. Because we have relatively few centres (n=14) compared to the number of patients (n= ≈1750), we expect any loss in efficiency from this method (compared to the random centre effects method) to be minimal. The linear mixed model described above will include an interaction between each covariate and whether bleeding volume was measured before and/or after randomisation. This gives treatment effect estimates that are identical to those from the standard ANCOVA model in the absence of missing data. We expect the covariates to affect bleeding volumes in different ways (e.g. older people are likely to have larger bleeds at baseline, more severely unconscious people (low GCS) are likely to have larger bleeds at baseline). In line with the CONSORT guidelines
^28^, we will also report the results from the linear mixed model without covariate adjustment to facilitate synthesis and comparability with other trials that may not include the same covariates.

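### The analyses offered as a check under MNAR exclude patients by baseline GCS, which leaves MAR in place and misses the within-GCS dependence the SAP itself suspects

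*SAP article*

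**What the plan says.** All of this stands in the SAP article, mostly in the section on missing data from scans not done before or after randomisation.

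- **Primary assumption:** "For the purpose of the primary analysis, we will assume missing data are MAR".
- **Promised check:** "we will conduct sensitivity analyses assuming missing data are MCAR or MNAR".
- **Definition:** data are MNAR when, after allowing for what was observed, "the reason for missing observations still depends on the unseen values". The SAP adds that it suspects this kind of dependence on haemorrhage volume inside GCS groups.
- **Under the MNAR label:** the plan is to "explore the possibility that missingness of the outcome data is related to prognostic characteristics as well as to the trial treatment". Two concrete analyses follow: "We will conduct sensitivity analyses excluding patients with a low pre-randomisation GCS who may have large haemorrhage expansion" and "We will conduct sensitivity analyses excluding patients with a high pre-randomisation GCS who may have smaller haemorrhage expansion". No cut-off is given for low or high.
- **Status of GCS:** the same section treats it as an observed baseline variable, and Primary analysis reports from the blinded data that "time from injury to CT scan, GCS, age and systolic blood pressure are significantly predictive of the pre- and post-randomisation bleeding volumes". Those covariates go into the primary mixed model.
- **Extent of missing scans:** Primary analysis says that fewer than 50% of patients have both scans. Sample size assumes that 47% are dropped, leaving 901 of 1700.

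**The concern.** Prognostic characteristics and treatment arm are observed. Missingness that depends only on them is MAR by the SAP's own definition. Restricting the analysis to part of the GCS range is conditioning on an observed covariate that the model already contains. Within the patients kept, unseen volumes are still taken to follow the observed ones.

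The SAP names routes to informative loss: death after expansion before a second scan, and no repeat scan in a patient who is stable. It also discusses how treatment might change either one. If such a route acts within GCS groups and differs by arm, the main estimate and both exclusions are biased together. Their agreement could then be taken for robustness to MNAR when they share the assumption in question.

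**Working it through.** **1. The plan's own figures.** 1700 × (1 − 0.47) = 901. The baseline-adjusted SD is 28 × √(1 − 0.6²) = 22.4 ml. For a 4 ml difference (28 v 24 ml), the standard error is 22.4 × √(4/901) = 1.49, so z = 2.68 and power is Φ(2.68 − 1.96) = 76%, as stated. These figures count patients with both scans. The split between missing pre- and missing post-randomisation scans is not given.

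**2. Why the exclusions follow the primary estimate.** Assumptions, none of them in the SAP:
- the log-odds of being scanned change by β per SD of the unseen post-randomisation log volume
- a fraction p is scanned post-randomisation
- the log SD is 1.0
- r is the variance left after baseline volume and GCS.

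To first order, the mean among scanned patients moves by β(1 − p)r, so the treatment estimate moves by (β_TXA − β_placebo)(1 − p)r. Dropping a GCS stratum does not alter this if β, p and r are similar across strata.

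**3. Size at p = 0.50 and |β| = 0.25 to 0.5, no true effect.** Simulation with 1,000,000 patients, pre/post slope 0.6 and GCS in the model:
- Opposite selection by arm: ratio 1.14 (|β| = 0.25) and 1.29 (0.5), each the same within 0.002 for all scanned, low-GCS third excluded and high-GCS third excluded.
- Placebo-only selection: 1.07 to 1.14 in all three.
- Same selection in both arms: about 1.00.
- Opposite selection with p = 0.75: 1.07 to 1.15, about half the bias, as the factor (1 − p) implies.

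The formula agrees: ln 1.14 = 0.131 = 2 × 0.25 × 0.5 × r gives r = 0.52, and halving 0.131 gives exp(0.066) = 1.07. If baseline explained only 0.6² = 36% of the variance (r = 0.64), the opposite-selection ratios would be about exp(0.16) = 1.17 and exp(0.32) = 1.38. With log SD 0.83 to 1.2 the simulated range is 1.11 to 1.36. A true ratio of 24/28 = 0.857 would appear as 0.857 × 1.14 = 0.98 to 0.857 × 1.29 = 1.11 under opposite selection.

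**4. When an exclusion does help.** A separate simulation used stronger selection (0.8 per log unit, about half unscanned, no true effect). Estimates are on the log scale:

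| Missingness | All scanned | Low GCS excluded | High GCS excluded |
|---|---|---|---|
| MAR given GCS | 0.001 | 0.001 | 0.002 |
| On unseen volume, same in both arms | 0.003 | 0.003 | 0.002 |
| On unseen volume, placebo only | 0.228 | 0.210 | 0.248 |
| On unseen volume, opposite by arm | 0.449 | 0.450 | 0.449 |
| On unseen volume, low-GCS placebo only | 0.079 | 0.000 | 0.120 |

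Only in the last row does an exclusion expose the bias.

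**5. What a tipping point would show.** If unseen volumes depart from MAR by d more in one arm than in the other, and a fraction f lacks a post-randomisation volume, the estimate moves by f × d. The planned effect is 4 ml, or ln(28/24) = 0.154 on the log scale. It is cancelled at:
- f = 0.25: d = 16.0 ml, ratio exp(0.154/0.25) = 1.85
- f = 0.47: d = 8.5 ml, ratio 1.39
- f = 0.50: d = 8.0 ml, ratio 1.36.

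The GCS exclusions contain no such parameter and cannot yield this figure.

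**The case against.** The best defence is that the SAP locates the feared losses at the ends of the GCS range: deaths among low-GCS patients and no repeat scan among high-GCS patients. If informative loss were confined to one end, removing that end would show it, as the last row of the table does. That stands. The check is incomplete rather than empty, and a reader who infers that the exclusions can detect nothing goes too far. But the SAP suspects dependence within GCS groups generally, and that is not reached.

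The size is also open to challenge. The SAP describes two effects of treatment on scanning as alternatives, each conditional on benefit. It does not describe selection running in opposite directions by arm at once, still less with no true effect. A reader might take 1.14 to 1.29 as the bias expected under the SAP's own mechanism. The document does not support that: the range is an unfavourable case, and selection alike in both arms gives about 1.00.

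Nor does the document show that more than half of the data are unseen. Its figures count patients lacking either scan, and patients with a single scan still contribute to the mixed model. It also plans comparisons of missingness by arm and by baseline variables, and concedes that MAR and MNAR are hard to tell apart. Those comparisons are useful diagnostics, but they do not estimate the treatment effect under MNAR. The SAP does not say that agreement will be reported as robustness to MNAR.

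**Conclusion.** The point holds in this form: the concrete analyses under the MNAR label do not relax MAR among the patients retained, and they do not address the within-GCS dependence that the SAP suspects. This follows from the SAP's definition, from GCS being observed and from its place in the primary model. One step is inferred. The SAP does not state the model for the subsets, but it specifies nothing other than the primary approach.

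Whether bias arises, and how much, is not known from the document. It requires selection on unseen volume that differs by arm. With log SD 1.0, 50% scanned post-randomisation and log-odds of 0.25 to 0.5 per SD, the null ratio is about 1.07 to 1.14 for placebo-only selection and 1.14 to 1.29 for opposite selection. The latter roughly halves if 75% are scanned. Such a bias could offset much or all of the planned 15% reduction, and the exclusions would be unlikely to reveal it. The change should be made. The finding does not show that the primary estimate is biased.

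**What to change.** 1. Relabel the two GCS exclusions as subset analyses under MAR, and state the cut-offs.
2. As the MNAR analysis, impute unseen post-randomisation log volumes by a delta-adjusted (pattern-mixture) method with arm-specific shifts. Treat patients who died unscanned separately from survivors who were not re-scanned.
3. Justify the range of shifts and fix it without reference to unblinded results. Trial status dates unblinding to 31 May 2019 and this third version to after a review of 6 June 2019, so the SAP should record how and by whom the range was set.
4. Report the tipping point, that is, the difference in shift between arms at which the conclusion changes, next to the fraction without a post-randomisation scan in each arm.
5. State how volume is interpreted for patients who died before a scan. Imputing a value for them is a choice of estimand and should be described as one.

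The cost is SAP wording, one further imputation analysis and the decision in item 5. Death within 28 days is already part of the composite outcome, so no new data are needed.

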### Between-centre effects

Randomisation into the CRASH-3 trial is stratified according to participating centres. We do not expect between-centre differences in unfavourable outcome to affect the chance of demonstrating a treatment effect in TBI
^35^. Nonetheless, the main effect of site will be included in the analyses. 

## Conclusion

This statistical analysis plan updates our previously published protocol
^18^. The main changes are: an increased sample size from 1,000 to a maximum of 2,000 patients, a comparison of intra-parenchymal bleeding expansion between treatment groups for the primary outcome, the use of covariate adjusted linear mixed models for the primary analysis and relevant secondary analyses, and restriction of the analysis of the primary and secondary outcomes (new and progressive bleeding) to patients treated within three hours of injury. We present our plan for the statistical analyses in advance of the database lock and un-blinding to guard against data dependent analyses. The CRASH-3 IBMS should provide reliable evidence on the effect of tranexamic acid on intracranial bleeding and infarction in TBI.

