### Sample size

We originally planned for the IBMS to be conducted in 1,000 CRASH-3 trial patients. This sample size was based on the reduction in bleeding volume seen with tranexamic acid in the CRASH-2 Intracranial Bleeding Sub-study (Perel
*et al.,* 2012). We expected a 15% reduction in intracranial bleeding with tranexamic acid (24ml tranexamic acid, 28ml placebo), a correlation of 0.6 between pre- and post-randomisation bleeding volumes, and a standard deviation of 28ml. This gave an unadjusted sample size estimate of 1542, which was reduced to 987 with adjustment (1542*(1-(0.6
^2^)) (Borm, 2007). 

Due to the large amount of missing data (only around half of patients are scanned both pre-randomisation and post-randomisation), we increased the sample size for the CRASH-3 IBMS to include around 1700 patients. This was the approximate maximum number of patients the scan assessor could feasibly collect data from before the CRASH-3 trial completed recruitment. Using the same expected treatment effect, standard deviation, correlation and baseline adjustment values as the original sample size calculation, this increased power to 95%. (at alpha=0.05) However, this calculation is not adjusted for missing data. If we assume that 47% of patients will be dropped from the analyses, this leaves a study with 901 patients scanned both pre-randomisation and post-randomisation. Using the same standard deviation (adjusted for baseline), correlation and baseline adjustment values as the original sample size calculation, a study with 901 patients would have 76% power to detect the expected treatment effect.

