The blinded data indicates that pre-randomisation and post-randomisation bleeding volumes are positively skewed. Because bleeding volumes are skewed, this data will be log transformed before entered into the linear mixed model. The anti-log of the treatment effect estimate and its corresponding 95% CIs will be presented to aid interpretation. The treatment effect estimates will provide an estimate of the relative increase or decrease in haemorrhage volume with tranexamic acid.

In the original protocol, we planned to analyse the primary outcome using ANCOVA. Since publishing the protocol, we learnt that less than 50% of patients were scanned both pre- and post-randomisation. Because the pre-randomisation mean bleeding volume of the observed data may be different from the true pre-randomisation mean bleeding volume, the estimates from the ANCOVA model may be biased. Compared to ANCOVA, linear mixed models are more powerful and typically less biased when there are missing data
^26^.

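### The plan gives two different maxima for the enlarged sample (about 1,700 and 2,000), and its 76% power assumes 53% of patients have both scans although it reports that fewer than half did

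*SAP article*

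**What the plan says.** **Size of the study.** The Sample size section starts from the earlier plan, "We originally planned for the IBMS to be conducted in 1,000 CRASH-3 trial patients", and then says "we increased the sample size for the CRASH-3 IBMS to include around 1700 patients". It adds that this was approximately the largest number the scan assessor could feasibly cover before the main trial finished recruiting. The Primary analysis section, when justifying fixed site effects, sets the 14 centres against a total: "compared to the number of patients (n= ≈1750". The Conclusion lists the main changes from the published protocol, the first of which is "an increased sample size from 1,000 to a maximum of 2,000 patients".

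**Share with both scans.** The Sample size section says loosely that around half of patients have both scans. It then makes the assumption numerical, "If we assume that 47% of patients will be dropped from the analyses", which leaves 901 patients with both scans and 76% power. The Primary analysis section, explaining why ANCOVA was dropped, says "we learnt that less than 50% of patients were scanned both pre- and post-randomisation".

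**Timing.** The Primary outcome section refers to blinded data already collected from 1700 patients. Under Trial status, the imaging data are said to have been recorded before 31 January 2019 and the trials unblinded on 31 May 2019. This third version answers clarification requests in a journal peer-review report submitted on 6 June 2019.

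**The concern.** The figure of 1,700 is presented as a practical limit and 2,000 as a maximum, both for the same increase. A reader of the final report cannot tell which of them was the planned size.

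The paired share is the more substantive of the two. The 901 is the only basis for the plan's power after allowing for missing scans, and it needs a share above one half. The plan elsewhere reports a share below one half and uses that fact to justify changing the primary model. The same quantity therefore appears on both sides of 50%, and the power statement uses the favourable side. What is at stake is the accuracy of a stated design figure, not the validity of any analysis.

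**Working it through.** **Inputs, all from the Sample size section unless noted**
- Effect: "We expected a 15% reduction in intracranial bleeding with tranexamic acid (24ml tranexamic acid, 28ml placebo", so the difference is 28 − 24 = 4 ml.
- Spread: "a correlation of 0.6 between pre- and post-randomisation bleeding volumes, and a standard deviation of 28ml".
- Alpha is 0.05. Sidedness is not stated; two-sided reproduces the plan's figures.
- Allocation is 1:1 (Introduction).
- Power for the original calculation is not stated in the article; 80% reproduces it.

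**Reproducing the plan's figures**
1. Unadjusted total: the two-sample normal formula with difference 4, SD 28 and 80% power gives 1,540. The plan has 1542, an immaterial difference.
2. Baseline adjustment: 1542 × (1 − 0.6²) = 1542 × 0.64 = 986.9. The plan has 987.
3. Adjusted SD: 28 × √(1 − 0.36) = 28 × 0.8 = 22.4 ml.
4. Power for total N: Φ(4 / (22.4 × √(4/N)) − 1.96).
   - N = 1,700: standard error 1.087, ratio 3.681, power 95.7%. The plan has 95%.
   - N = 901: standard error 1.493, ratio 2.680, power 76.4%. The plan has 76%.
5. Paired count: 1,700 × (1 − 0.47) = 1,700 × 0.53 = 901, as stated.

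A noncentral-t check gives 95.7% and 76.3%. The section's arithmetic is sound on its own inputs.

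**Setting the sizes side by side**
- 2,000 − 1,700 = 300 patients, and 2,000 / 1,700 = 1.176. The Conclusion's maximum is 17.6% above the feasible maximum, more than an approximation would cover.
- 1,750 / 1,700 = 1.029. Both figures are marked approximate, so this 2.9% gap is not a contradiction.

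**Setting the paired shares side by side**
- 901 / 1,700 = 53.0% and 901 / 1,750 = 51.5%. Neither is below 50%, so using the 1,750 does not rescue the 901.
- Fewer than 50% of 1,700 means fewer than 850 pairs. At N = 850 the standard error is 1.537, the ratio 2.603 and the power 74.0%, so the paired-only power is below about 74%.
- With 1,750 instead, there are fewer than 875 pairs and power is below about 75.2%.
- Loss against the plan's figure at N = 1,700: 76.4 − 74.0 = 2.4 points at the 50% bound, and more if the share was lower. The article does not say how far below 50% it was.

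**The case against.** **The 2,000 may be a ceiling.** A ceiling of 2,000 with about 1,700 expected would be coherent. That is possible, but the article does not say so, and it already uses the word maximum for the 1,700. The ambiguity therefore stands. A reader might go further and infer that a study of 1,700 falls 15% short of plan. That does not follow, because being below a stated maximum is not a shortfall.

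**The 901 is conditional and the observation undated.** The 47% is introduced as an assumption. The article also draws on different data snapshots: the Introduction cites about 1,000 patients so far, the Primary outcome section 1700. The share below 50% may not be the final one. This is fair, and it is why the result is given as a bound. Still, the article does not attribute the two shares to different snapshots, and the assumption is more favourable than what the plan says it had learnt.

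**The paired count is not the analysed number.** This stands. The linear mixed model was chosen so that patients with only one of the two scans also contribute. A reader might infer that the primary analysis has under 74% power. The documents do not support that, since the figure describes a paired-only analysis. The plan's 76% is subject to the same limit.

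**Only one paired power is stated.** This also stands. Multiplying 53% by 2,000 gives 1,060 pairs and 82.8% power, so a reader might infer that the plan's statements span 74% to 83%. The plan attaches no paired count or power to the 1,750 or the 2,000, so that spread is not something it asserts.

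**Reporting is already promised.** Trial profile and the missing-data section commit to reporting scan availability in the results. That helps the final report but does not correct the planning figures.

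**Conclusion.** Two inconsistencies hold on the text. The enlarged sample has two unreconciled maxima, about 1,700 and 2,000. The missing-data power of 76% rests on 53% of patients having both scans, against a reported share under 50%. At 1,700 patients, the reported share implies fewer than 850 pairs rather than 901, and a paired-only power below about 74%.

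This takes the plan's difference, SD, correlation and alpha as given, assumes a two-sided test, and assumes that the reported share applies to the full 1,700. There is no calculation error in the Sample size section, and the approximate 1,750 only needs aligning. No model, estimand or decision rule depends on these counts. The effect is about 2 points of stated power or more, and the severity is minor.

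**What to change.** 1. Use one sample size in the Sample size section and the Conclusion, and align the approximate total in the Primary analysis section with it. Delete the maximum of 2,000, or say explicitly that it is a ceiling and how it relates to the 1,700.
2. Replace the 47% and the 901 with the observed paired-scan count pooled over arms. If that is not used, choose a share consistent with the Primary analysis section. If the two shares come from different data snapshots, say so.
3. Restate the 76% from that count. Note that it is a paired-only figure, while the mixed model also uses patients with one scan.
4. Label the edit as a clarification made after the 31 May 2019 unblinding, using only counts pooled over arms.

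The cost is wording and a slightly less favourable power figure. Pooled scan counts need no treatment allocation, and no analysis changes.
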